**Figure 3 F3:**
[figure not shown]
Schedule of enrollment, interventions, and assessments (using the SPIRIT 2013 statement). AE = adverse event, BD-QoL = quality of life for Behcet disease, CRP = C-reactive protein, ESR = erythrocyte sedimentation rate, GDPSF = Glycyrrhizae Decoction for Purging Stomach-Fire, GGT = gamma-glutamyl transpeptidase, Ig = immunoglobulin, MAI = mucocutaneous activity index.

IBM SPSS 21 Statistics will be applied for the analysis. Measurement data that followed normal distribution will be recorded as mean ± SD and analyzed by ANOVA or *t* test, otherwise, Kruskal–Wallis will be applied. Count data will be analyzed by χ^2^ test. The statistical significance level was set at *P* < .05 for all the tests.

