### Primary outcome measures

3.1

As the oral and genital ulceration, skin lesions (erythema nodosum) are most common complaints in BD patients. We select a mucocutaneous activity index (MAI) in BD created by Mumcu et al.^[14]^ In this MAI:Presence of the lesion was coded as 1 for actives and 0 for inactives (0 vs 1 point)Pain was evaluated by 100 mm-visual analogue scale (VAS; 0: no pain–100: severe pain) by patients. Then, the VAS score was categorized to calculate the score as follows: ≤10: 0; 11–20: 1; 21–40: 2; 41–60: 3; 61–80: 4; 81 and over: 5 points.Functional status was evaluated by a 5-point Likert-type scale: none of the time (0 points), little of the time: 1 point, some of the time: 2 points, most of the time: 3 points and all of the time: 4 points. Mean score was used in the index (Table 2).

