**Table 2 T2:**
[figure not shown]
Mucocutaneous activity index and its subscales in BD.

Based on the follow-up of the MAI and other-related symptoms in BD, the remission ratio after treatment will be accessed. The remission degree will be divided into 4 levels:Cured: All of the BD manifestations disappeared, rare relapse (less than 2 times a year) after stop treatment for more than 1 year.Complete remission: Most of the BD manifestations disappeared (MAI reduce ≥3 points), occasionally relapse (less than 4 times a year), but could easily manage by the treatment.Partial remission: Some of the BD manifestations disappeared; the frequency of relapse is less than before treatment.No effect: BD manifestations not respond to the treatment, relapse during the treatment.

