### Statistical analysis

4.2

This is an 18 months clinical trial, in which participants will receive treatment for 6 months and accept a 12 months follow-up. During their treatment, participants will visit investigators every 4 weeks 5 times in all. Their clinical manifestations (MAI), blood tests, thalidomide dosage in thalidomide, and integrative groups will be assessed. Participants will receive 2 times of follow-up for 12 months after treatment, their remission levels, quality of life, and satisfactory levels will be assessed. Figure 3 summarizes the study schedule of enrollment, interventions, and assessments according to the SPIRIT 2013 statement. The data of assessments on each intervention group before and after treatments will be collected and analyzed through historical control, while between groups through intergroup control method.

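### The only test named for non-normal data, Kruskal–Wallis, is for independent groups and does not fit the planned before-after comparisons of the same patients

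*Protocol article*

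**What the plan says.** Section 4.2 (Statistical analysis) sets out two kinds of comparison. Within groups: "The data of assessments on each intervention group before and after treatments will be collected and analyzed through historical control". Between groups: "while between groups through intergroup control method".

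The tests follow in the same section, below the caption of Figure 3: "Measurement data that followed normal distribution will be recorded as mean ± SD and analyzed by ANOVA or" a t test. The text does not say whether that t test is paired. For measurement data that are not normal, "otherwise, Kruskal–Wallis will be applied". For categories, "Count data will be analyzed by" a chi-square test. All tests use the 0.05 level.

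Section 3.1 (Primary outcome measures) builds the MAI from presence codes of 0 or 1, a pain item ("Then, the VAS score was categorized to calculate the score as follows", giving 0 to 5 points) and a mean functional score. It then adds remission: "The remission degree will be divided into 4 levels", running from cured to no effect. Complete remission includes a fall in MAI of at least 3 points.

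**The concern.** Values taken before and after treatment in one group come from the same patients, so they are paired. The single method fixed for non-normal measurement data treats its samples as independent. This is a mismatch between two things the article states, so it is not a detail left to a fuller document. Section 4.1.1 names the before-after effect of the decoction as one of the study's aims, so the affected comparison is not a side issue.

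The fallback could well be needed. The MAI is built largely from coded categories, and inflammatory markers such as CRP and ESR are often skewed. A test that ignores positive within-patient correlation uses too large a standard error. The P values come out too large and real changes are missed.

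Two lesser points concern efficiency. The tests named for comparing groups contain no term for baseline MAI. Chi-square, the only test named for categories, would ignore the order of the four remission levels if they were compared as one outcome.

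**Working it through.** **Inputs from the document.** Section 4.1.1 gives 50 patients per group and 20% dropout, so 50 × (1 − 0.20) = 40 evaluable per group. It gives no power, effect size or standard deviation, so there is no power figure to reproduce. The level is 0.05 (section 4.2), taken as two-sided.

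**Assumptions.** Before-after correlations r of 0.3, 0.5 and 0.7, the effect sizes and the remission probabilities below are assumed. The document gives none of them.

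**1. Independent-groups test on paired data, normal theory.** With equal variances σ², the variance of the mean change is 2σ²(1 − r)/n. An independent-groups test uses 2σ²/n. The standard error is therefore overstated by 1/√(1 − r), and the true error rate is 2 × [1 − Φ(1.96/√(1 − r))].
- r = 0.3: factor 1/√0.7 = 1.20; true error rate 1.9%.
- r = 0.5: factor 1/√0.5 = 1.41; true error rate 0.6%.

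**2. The same question for Kruskal–Wallis itself.** Skewed (log-normal) paired data were simulated, 40 patients, 4,000 runs per setting. The alternative is a shift of 0.4 SD on the log scale. The signed-rank test was applied to log differences.

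| r | Error rate, Kruskal–Wallis | Error rate, signed-rank | Power, Kruskal–Wallis | Power, signed-rank |
|---|---|---|---|---|
| 0.3 | 1.9% | 4.8% | 38% | 52% |
| 0.5 | 0.9% | 4.9% | 38% | 67% |
| 0.7 | 0.0% | 4.4% | 34% | 87% |

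The two approaches agree at r = 0.3 and are close at r = 0.5 (0.6% and 0.9%). With no correlation (r = 0) the two tests perform alike: error rates 5.2% and 5.1%, power 42% and 41%. The loss therefore comes from ignoring the pairing.

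**3. Baseline in the between-group comparison.** Adjusting an end-of-treatment value for baseline multiplies its variance by 1 − r². At r = 0.5 this is 1 − 0.25 = 0.75, a 25% cut, and 40/0.75 = 53, so 40 per group act like 53. For a difference of 0.5 SD with 40 per group, power for end values alone is 61%. With ANCOVA it is 65%, 73% and 88% at r = 0.3, 0.5 and 0.7.

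**4. Ordered remission levels.** Three arms of 40 were simulated, with two arms at assumed levels of 10/30/35/25% and one arm better by a common odds ratio (4,000 runs per setting).

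| Odds ratio | Power, chi-square | Power, rank test |
|---|---|---|
| 2 | 25% | 39% |
| 2.5 | 42% | 62% |
| 3 | 60% | 78% |
| 4 | 83% | 94% |

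With no difference between arms the error rates are 4.2% and 4.4%. Chi-square is valid here; it only gives up power, by about 12 to 20 points.

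**The case against.** The strongest reply is that ANOVA with Kruskal–Wallis as its fallback is a standard and correct pair for three independent arms, and that the t test named for normal data can be the paired one. Both points stand. The defect is confined to non-normal before-after data, and it bites only if Kruskal–Wallis is then used on them as written. Whether the MAI will be non-normal is not known: Table 2 is not shown, and a mean score enters the index. The within-group comparisons are also uncontrolled, so they carry less weight than the randomised ones.

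Several stronger readings are tempting, and the document does not support them.
- A reader might infer that baseline MAI is never used. It is used in the before-after comparison and in the 3-point rule for complete remission. What is true is that no baseline term is named for comparing groups. An unadjusted randomised comparison is valid, a condensed article may leave adjustment to a fuller plan, and the text does not say whether ANOVA is run on end values or on changes.
- A reader might infer that the four remission levels are assigned to chi-square. Section 4.2 speaks only of count data, and section 2.2 speaks of comparing complete and partial remission rates and an ineffective rate. Chi-square suits such rates.
- A reader might expect chi-square to fail through sparse cells. No check showed an inflated error rate.
- A reader might fear false claims of benefit. The error from ignoring the pairing goes the other way.

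**Conclusion.** The point holds in limited form. Section 4.2 plans paired comparisons and fixes an independent-groups test as the only method for non-normal measurement data. Followed literally, this gives P values that are too large. The true error rate is about 1.9% at an assumed correlation of 0.3 and about 0.6% to 0.9% at 0.5. Power falls by about 14 points (52% to 38%) and 29 points (67% to 38%) respectively, for an assumed shift of 0.4 SD on the log scale in 40 patients. The size depends on the correlation, which the document does not give; the direction does not change for any positive correlation.

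Baseline adjustment and an ordinal method for remission are improvements in precision, not corrections of invalid tests. The first is worth a 25% variance reduction at an assumed correlation of 0.5. The second is worth roughly 10 to 20 points of power under an assumed proportional-odds shift, and applies only if the four levels are compared as one outcome.

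**What to change.** In section 4.2, tie each test to its comparison:
- Before-after change within a group: Wilcoxon signed-rank test, or paired t test if the differences are normal, reported as descriptive.
- Independent groups: keep ANOVA, and Kruskal–Wallis where data are not normal.
- Between-group MAI at the end of treatment: ANCOVA with group and baseline MAI.
- Remission, if the four ordered levels are compared as one outcome: a rank test or proportional-odds regression. Keep chi-square for binary rates.

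The cost is a few lines of wording. No extra data or visits are needed, since baseline is already measured, and the named SPSS version runs all of these methods. The wording should be settled before the allocation is unblinded.

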### Study design

2.2

This is a single center, double-blinded, randomized, and controlled, parallel-group study. Figure 1 depicts a flow chart of the study. Patients enrolled in this study will randomly be assigned into 3 different groups with respective treatment. Clinical manifestations, blood inflammatory index including erythrocyte sedimentation rate (ESR), C-reactive protein (CRP), and some of the blood biochemical tests will be checked before treatments started (baseline) and will be reexamined on week 4, 8, 12, 18, 20, and 24 during 6 months of treatment to assess the effectiveness and safety. Try to follow up every participant in another 12 months to compare satisfactory rate, complete and partial remission rate, and ineffective rate in different treatment groups.

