### Randomization and blinding

2.5

To minimize selection bias, all eligible patients will be randomized in a 1:1:1 ratio to the 3 different intervention groups. Patients will be allocated to each group in turn based on the turn of patients’ identification number generated by Hospital Information System (HIS). Randomization will be performed by a professional, independent statistician who is not involved in the recruitment process of this study. Randomization information will be kept secure in Good Clinical Practice (GCP) Center of Huadong Hospital, neither patients nor doctors know the specific group a participant joined in, and will not be opened until after statistical analysis or in the case of a medical emergency.

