### Secondary outcome measures

3.2

Blood inflammatory index including ESR, CRP, and some of the blood biochemical tests such as IgA, IgD, IgE, and IgM, and gamma-glutamyl transpeptidase will be checked before treatments started (baseline) and will be reexamined on week 4, 8, 12, 18, 20, and 24 during 6 months of treatment to assess the effectiveness.

Satisfactory ratio on effectiveness: Every half a year, the controlling on the BD symptoms will be evaluated by patients’ own intuition. VAS for pain is mimicked by the satisfaction scale (Fig. 2).

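### Every test is judged at P < .05 while two primary measures stand unranked across three groups, so the false-positive risk on the primary outcomes is not held at 5%

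*Protocol article*

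**What the plan says.** The error rate is fixed in section 4.2 (Statistical analysis), in the paragraph after the Figure 3 caption: "The statistical significance level was set at *P* < .05 for all the tests". The same paragraph names ANOVA or a t test for normally distributed measurements, Kruskal–Wallis otherwise, and chi-squared for counts.

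Section 3.1 (Primary outcome measures) introduces one instrument, "We select a mucocutaneous activity index (MAI) in BD", and then under the same heading adds a second measure: "Based on the follow-up of the MAI and other-related symptoms in BD, the remission ratio after treatment will be accessed". That second measure has four levels, and neither is put first.

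Section 2.5 sets out the groups: "all eligible patients will be randomized in a 1:1:1 ratio to the 3 different intervention groups". On timing, section 2.2 says that clinical manifestations and blood tests "will be reexamined on week 4, 8, 12, 18, 20, and 24 during 6 months of treatment", which is six occasions. Section 4.2, which places the MAI at the treatment visits, says "participants will visit investigators every 4 weeks 5 times in all". Two follow-up assessments come after treatment.

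Section 2.1 puts GDPSF first and the combination second among the objectives, but gives no comparator, outcome or time point. Section 4.2 foresees both within-group before/after analyses and between-group analyses, and does not say which decides the trial.

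**The concern.** A 5% threshold protects a conclusion only when it is known in advance which test supports that conclusion. Here the reader cannot tell whether the trial succeeds on the MAI or on remission, at week 24 or at another visit, or for GDPSF against thalidomide, the combination against thalidomide, or GDPSF against its own baseline. The threshold is granted to all of them equally, so any one small P value could be presented as the answer. The 5% then describes no stated claim.

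What is at stake is how a positive result would be read. The end of the Background, section 2.1 and the close of the Discussion point to effectiveness and to an evidence-based option for patients. A chance finding on one of several unranked tests could be carried into that message.

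**Working it through.** **The article's own figures.** Section 4.1.1 gives 50 per group and 20% dropout: 3 × 50 = 150 recruited, and 50 × (1 − 0.20) = 40 evaluable per group. These agree. The only stated error rate is 0.05 per test. Sidedness is not given, and two-sided is assumed.

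**Upper bound.** For k independent tests at 0.05, the chance of at least one false positive is 1 − 0.95^k.
- k = 2 (two measures, three-group test, one time point): 1 − 0.95² = 9.75%.
- k = 6 (two measures × three pairs): 26.5%.
- k = 18 (three pairs × [five MAI visits + remission once]): 60.3%.
- k = 21 (the same with six MAI visits): 65.9%.

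**Allowing for correlation.** Pairs share groups, visits share patients, and remission is built on the MAI: section 3.1 defines complete remission partly by an MAI drop of at least 3 points. Independence therefore overstates the risk. I simulated trials with no true difference: 40 per group, normal data, correlation 0.6 between any two MAI visits (assumed), and 10,000 trials per setting. A normal score stands in for remission, with a range of assumed correlations to the last MAI. Chance of at least one P < .05:

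| Tests run | Corr. 0 | 0.3 | 0.6 | 0.9 |
|---|---|---|---|---|
| Both measures, one time point, three-group tests | 9.7% | 9.5% | 8.5% | 6.8% |
| Both measures, one time point, all pairs | 22.6% | 22.4% | 20.1% | 16.3% |
| MAI at 5 visits + remission, three-group tests | 21.8% | 20.7% | 19.7% | 18.7% |
| MAI at 6 visits + remission, three-group tests | 22.7% | 22.5% | 21.4% | 20.3% |
| MAI at 5 visits + remission, all pairs | 43.8% | 43.7% | 41.3% | 38.8% |
| MAI at 6 visits + remission, all pairs | 47.0% | 46.5% | 44.6% | 42.1% |

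Because remission rests on the MAI, a correlation of exactly 0 is not plausible. From 0.3 to 0.9 the ranges are about 7–10% (three-group tests, one time point), 16–22% (all pairs, one time point) and 39–47% (all pairs, five or six visits).

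**Sensitivity to the assumed 0.6.** With one common correlation among all seven measures (six MAI visits and remission), the all-pairs figure is 60% at 0, 54% at 0.3, 47% at 0.5, 38% at 0.7 and 27% at 0.9. With three-group tests only it runs from 30% down to 13%.

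**Check of the remedy.** One named pair, measure and time point gives about 5% in the same simulations.

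None of these figures counts the before/after tests, the follow-up assessments or the secondary outcomes.

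**The case against.** Several points on the other side have force.

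- *A reader might infer that a false positive is likely.* The article does not support that. Above 50% requires every pair tested at every visit with low correlation. The article names omnibus tests for three groups, does not say what the t test is for, and nowhere states that all pairs or all visits will be tested. Measuring the MAI at a visit is not the same as testing it there, and the talk of data before and after treatment points towards fewer tests. The higher figures show what the wording permits, not what it announces.
- *An omnibus test used as a gate protects three groups.* True within one measure and one visit: the three-group figures then apply. The article does not say that it is used that way, and a gate does nothing across two measures.
- *The study is a pilot.* Section 4.1.1 gives feasibility of a larger trial as its purpose, and the Discussion repeats the pilot label. This softens the consequence. It does not remove it, because the primary objective in section 2.1 is effects and safety, and the results are to be tested for significance.
- *A separate analysis plan may deal with multiplicity.* It may, so no missing adjustment is alleged. The point rests on what is stated: one threshold for every test and two unranked primary measures. A later adjustment would have to override that sentence.
- *The blood markers add many more tests.* Section 3.2 labels them secondary, and testing each at every visit would again be an assumption. They are left out of the figures.

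**Conclusion.** The point stands in a bounded form. On the schemes examined, two unranked primary measures with every test at 0.05 put the chance of a false positive on the primary outcomes above 5%. How far above depends on choices the article leaves open: modestly so with three-group tests at one time point, and several times the nominal rate with all pairs at all visits. The sizes rest on 40 evaluable per group, normal data and the assumed correlations. They fall as remission follows the MAI more closely or as visits become more alike.

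This should be corrected before the allocation code is opened. It does not show that any particular result will be false, or that the trial is unsound as a feasibility study.

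**What to change.** Replace the blanket sentence in section 4.2 with a named primary test. One workable version: the primary outcome is the MAI at end of treatment, adjusted for baseline. GDPSF is compared with thalidomide first at two-sided 0.05, and integrative with thalidomide is tested only if the first is significant. Holm across the two comparisons is an alternative. This follows the order of objectives in section 2.1 and uses the control named in the Discussion. Choosing remission instead of the MAI would also answer the point, provided that one measure, time point and order are fixed.

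Treat the other primary-heading measure, the other visits, blood markers, quality of life and satisfaction as secondary or exploratory, reported as estimates with 95% confidence intervals. If the sponsor means the whole trial to be a feasibility pilot, say that all comparisons are exploratory and drop the threshold. The five and six visit counts in sections 4.2 and 2.2 must be reconciled in either case.

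Cost: wording only, with no extra patients. Fewer results can be called significant. The fixed sequence costs the first comparison no power, but the second cannot be claimed if the first fails. Under Holm the smaller P value must reach 0.05/2 = 0.025. With 40 per group, the standardised difference detectable at 80% power at that level is (2.241 + 0.842) × √(2/40) = 0.69, against (1.960 + 0.842) × √(2/40) = 0.63 at 0.05.

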## Discussion

5

In this pilot study, we chose mucocutaneous type of BD patients as out eligible patients, because, if the disease involved vital organs already, intensive treatments will be needed, which makes the simple application of GDPSF or thalidomide not safe for patients. The symptoms caused by the disease especially recurrent oral and genital ulceration cause pain and decrease quality of life in BD patients, lead them suffer physically and psychologically.^[20]^ As a result, it is not proper to give a BD patient placebo treatment as a control. Thalidomide is one of the most common options to erase symptoms in adult BD patients. It provided a useful therapeutic option in severe oral and genital ulceration, which had not responded to other therapies.^[20]^ Therefore, besides of historical control, thalidomide treatment group will set as a control.

Traditional Chinese medicine (TCM) gained afflatus from war that similar principles dominate in both military and medicine, which is to prescribe drugs as monarch, minister, assistant, and guide in a formula according to military action strategies or country governance. In the formula of GDPSF, the *G uralensis* plays the role of monarch, which targets the disease or main symptoms suffered. There has been numerous of in vivo and in vitro researches on antiinflammatory activity from *G uralensis*.^[21,22]^ Extracts from *S baicalensis* also showed activity of antiinflammation, antitumor, and attenuates oxidant stress.^[23,24]^ Researches on *P ternate* shows antidepression, gastrointestinal regulation,^[25,26]^ and effects on blood pressure.^[27]^*C chinensis* shows activity of antimicrobial,^[28]^ while mycobacterial such as *Streptococcus* were though as one of the risks to induce the onset of oral ulcers in BD.^[29]^ The multiple functions of *S baicalensis*, *C chinensis*, and *P ternate* can be used to assistant monarch to enhance the effectiveness for the main disease or symptoms, play a role of minister. Potential side effects in the formula based on TCM would relieve by *P ginseng*, which has been richly investigated. As the chemical elements are extremely complex in n herb formula, and considering the relation between parts and whole, it is impossible to illustrate the GDPSF pharmaceutical actions through current researches on extractives. Good news is the compound formula is gaining attention.^[30]^

There is extensive literature on the chemical constituents and bioactivities of *P ginseng*. The chemical constituents isolated and detected from ginseng show the biological activities of immunoregulatory activity, neuroregulation activity, wound and ulcer healing activity, etc.^[31]^ Thus, we hypothesize, GDPF may reduce the events like leukopenia, peripheral neuropathy caused by thalidomide. Therefore, in this research, we set an integrative group to combine the application of GDPSF and thalidomide, hopefully to enhance the treatment outcomes and reduce side effects.

The Silk Road is an ancient trading route that were for centuries central to cultural interaction originally through regions of Eurasia connecting the East and West and stretching from the Korean peninsula and Japan to the Mediterranean Sea. Underling the guideline of One Belt and One Road policy of Chinese government, we hope TCM can serve more people in the world. Through this ROTs, we hope to provide a new evidence-based treatment option for BD patients.
